### Data management

Data entry will be checked using a 5% double-entry procedure. Anonymised measures data are stored electronically on a University of Sheffield password-protected secure server, with only named people having access. No patient personal details are stored electronically. Paper copies of measures are stored in locked filling cabinets behind two locked doors. Patient contact information, on paper, is stored in different locked filling cabinets, in a different office, again behind two locked doors. The trial adheres to the University of Sheffield Ethics Policy Governing Research Involving Human Participants, Personal Data and Human Tissue (version 6). Information Governance toolkit details for electronic data storage are as follows: organisation code 8D715-SHR, version 13, 2015/16; reviewed grade satisfactory (level 2 or above).

### Statistical methods

Statistical analyses will be carried out by a statistician and senior statistician from the Clinical Trials Research Unit (CTRU). Neither will be involved in the administration of the trial and both will be blinded to the randomisation and assignment. The two treatment arms will be coded as non-identifiable variables to minimise potential biasing in analyses.

### Primary analysis

The primary analysis will adhere to a Statistical Analysis Plan (SAP) devised by an independent statistician under the guidance of the senior medical statistician. The SAP was informed by the International Conference on Harmonisation topic E9 [53], reference to the literature (e.g., [54]) and applicable standard operating procedures from the University of Sheffield Clinical Trials Research Unit (CTRU). Non-inferiority of counselling to CBT will be concluded if the CI lies entirely above the non-inferiority limit of −2 units (i.e., that a difference as large as 2 units in favour of CBT has been ruled out).

In contrast to superiority trials, the ITT analysis is anti-conservative (i.e., it underestimates the treatment effect) when looking at non-inferiority. Specifically, if an intervention is not delivered as fully planned by the protocol the ITT analysis dilutes the treatment difference and therefore raises the risk of having the groups look artificially similar (and hence CfD being artificially non-inferior to CBT). Given the pragmatic nature of the trial the ITT will remain the primary analysis population, but additional consideration will be given to other analyses that exclude participants who did not receive the intervention as planned. It should also be noted there is a general lack of guidance regarding the choice of the primary analysis population for non-inferiority trials [55].

The additional analysis populations are:An objective per-protocol analysis (PP1) that excludes participants who receive fewer than four sessions within 6 months of randomisation and/or who switch treatment arms within 6 months of randomisation.A case-review per-protocol analysis (PP2) in which participants are assessed on a case-by-case basis for the number and timing of sessions, additional therapies received and therapist adherence to principles of CBT or CfD. This will necessarily be unblind to treatment group but will be blind to outcome data.Complier-adjusted causal effect (CACE) models in which participants who undergo their intervention in accordance with protocol are compared to those in the comparator group who are “likely” to have done so (based on statistical modelling) had they been randomised to receive it. Two CACE analyses will be undertaken, one of which excludes “non-receivers” of CBT and the second removing “non-receivers” of CfD.

A fuller description of these analyses is provided in the Statistical Analysis Plan.

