### Clinical supervision and adherence/competency monitoring

We will monitor and assess adherence and competence through two methods: clinical supervision and rating of audiotapes of therapy sessions. The benchmark adherence/competence rating scales for each therapy condition will be used: for CfD, the Person Centred and Experiential Psychotherapy Rating Scale (PCEPS) [33] and, for CBT, the Cognitive Therapy Scale-Revised (CTS-R) [34, 35].

Clinical supervision is carried out as standard in line with IAPT guidelines, ensuring that only qualified CfD supervisors supervise CfD-trained counsellors. Supervisors use a simplified four-item version of the Person Centred and Experiential Psychotherapy Scale (PCEPS) to monitor adherence together with general competency at their supervision sessions during the course of the trial. For any one patient, this is carried out at sessions 2, 6 and 12 (should the patient receive that number of sessions). This procedure ensures that adherence and competency data are available for all patients in the trial. CBT supervision mirrors the CfD process using a simplified four-item version of the Cognitive Therapy Scale-Revised (CTS-R) completed by the supervisor at sessions 2, 6 and 12. These session forms are referred to as the Session Adherence and Competence Scale (SACS) for CfD (SACS-CfD) and for CBT (SACS-CBT).

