#### Primary Outcome

##### Patient Health Questionnaire-9 (PHQ-9) [39]

The primary outcome measure is the PHQ-9, a brief (9-item) self-report 4-point Likert-type scale measure of depression. Items correspond to each of the nine DSM-5 criteria for depression [40]. Items ask patients to rate how often they have been affected by symptoms (of depression) over a 2-week time period prior to completing the questionnaire.

Individual item scores range from 0 (*“not at all”*) to 3 (*“Nearly every day”*) with total PHQ-9 scores ranging from 0 to 27. Scores of 10 and above are demarcated as clinical scores. Scores of 5–9, 10–14, 15–19 and 20–27 are classified as reflecting mild, moderate, moderately severe and severe levels of depression respectively. The measure has an internal reliability of 0.89 and a test-retest reliability of 0.84 across 48 h. The PHQ-9 is mandated by the IAPT service and is completed by patients at each session attended along with other mandated measures within the IAPT minimum data set (MDS) [41].

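### The case-review per-protocol set (PP2) is declared necessarily unblind as a whole, although only the adherence criterion, and additional therapy that is the other arm's treatment, need the arm to be known

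*Protocol article*

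**What the plan says.** All of the following is in the protocol article.

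- **Primary analysis.** The section warns that ITT can make the arms look too alike in a non-inferiority trial. It still keeps ITT as primary: "Given the pragmatic nature of the trial the ITT will remain the primary analysis population". The additional analyses are offered in response.
- **PP1**, labelled objective, "excludes participants who receive fewer than four sessions within 6 months of randomisation and/or who switch treatment arms within 6 months of randomisation".
- **PP2** is a case review in which "participants are assessed on a case-by-case basis for the number and timing of sessions, additional therapies received and therapist adherence" to the principles of the assigned therapy. On masking: "This will necessarily be unblind to treatment group but will be blind to outcome data".
- Two **CACE** models follow. The section closes: "A fuller description of these analyses is provided in the Statistical Analysis Plan". That plan is not shown.
- **Clinical supervision and adherence/competency monitoring.** Each therapy has its own scale, PCEPS for CfD and CTS-R for CBT, with a short supervisor-completed form for each arm. For CfD: "Supervisors use a simplified four-item version of the Person Centred and Experiential Psychotherapy Scale (PCEPS) to monitor adherence"; the CBT process mirrors this.
- **Blinding.** A patient's assignment is to be unmasked only when the data and ethics committee specifically directs it. **Statistical methods** keeps both statisticians blinded.
- **Primary Outcome.** The PHQ-9 "is completed by patients at each session attended".

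**The concern.** PP2 is the only additional population whose stated criteria include additional therapies and therapist adherence. It is therefore the analysis that looks most directly at whether each therapy was delivered as planned, which is the weakness of ITT that the section itself describes. It is also the most discretionary of the sets.

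A reviewer who knows the arm may, without intending it, treat a borderline patient (few sessions, a long gap, some other therapy) more strictly in one arm than in the other. Blinding to outcome stops selection on results. It does not stop uneven strictness. If the borderline patients differ in outcome from the rest, uneven exclusion moves the PP2 difference, and agreement or disagreement with ITT becomes harder to interpret. The exposure is avoidable for every criterion that does not need the arm.

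**Working it through.** **1. Which criteria need the arm?**

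| PP2 criterion | Arm needed? | Reason |
|---|---|---|
| Number of sessions | No | A count. PP1 already applies one by rule, and Treatment delivery sets the same maximum of 20 sessions in both arms. |
| Timing of sessions | No | Dates relative to randomisation. |
| Additional therapies | Mostly no | A dated entry is enough, unless the extra therapy is the other arm's treatment, where naming it reveals the arm. |
| Therapist adherence | Yes | The principles and the rating scales differ by therapy. |

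So *necessarily* holds for the fourth criterion and for part of the third, not for the review as a whole.

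**2. The plan's own figure.** Inputs from Sample Size: margin 2, SD 6.9, true difference 0, one-sided 2.5%, power 90%.

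n per arm = 2 × [6.9 × (1.960 + 1.282) / 2]² = 250.13. At 250 per arm the power is 89.99%. The stated 250 per arm is reproduced and does not depend on PP2.

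**3. Illustration of the possible shift.** Assumptions, not in the documents: k more patients are excluded from one arm of 250 than from the other, and each lies 6.9 points (one SD) below the arm's mean improvement.

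- Shift in that arm's mean: s = 6.9k / (250 − k)
- SE of the difference: 6.9 × √[1/250 + 1/(250 − k)]
- Exclusions from CfD: chance that PP2 shows non-inferiority at a true difference of −2 = Φ(s/SE − 1.96)
- Exclusions from CBT: power of PP2 at a true difference of 0 = Φ((2 − s)/SE − 1.96)

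| k | s | s as share of margin 2 | SE | False non-inferiority (excluded from CfD) | Power (excluded from CBT) |
|---|---|---|---|---|---|
| 0 | 0 | 0% | 0.617 | 2.5% | 90% |
| 5 | 34.5/245 = 0.14 | 7% | 0.620 | 4% | 85% |
| 10 | 69/240 = 0.29 | 14% | 0.624 | 7% | 78% |
| 20 | 138/230 = 0.60 | 30% | 0.630 | 16% | 60% |

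For k = 20: 0.60/0.630 − 1.96 = −1.01, and Φ = 0.16; 1.40/0.630 − 1.96 = 0.26, and Φ = 0.60. Losing 20 patients with no shift would leave power at Φ(2/0.630 − 1.96) = 0.89, so nearly all of the fall comes from the shift.

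**4. Range under other assumptions.** If an extra share f of one arm is excluded and those patients do g points worse than the retained ones, the shift is f × g. For f from 5% to 20% and g from 2 to 6.9 points, it runs from 0.05 × 2 = 0.10 to 0.20 × 6.9 = 1.38 points. If the excluded patients did better than average, for instance by stopping early because they had improved, the sign would reverse.

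**5. Blinding set against PP2.** Blinding makes unmasking conditional on the committee's direction. PP2 plans it in advance and does not mention the committee. The two can be made compatible, but the article does not connect them.

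**The case against.** The case for leaving the plan alone has real weight.

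- **A case review with one arm-specific criterion is unblind as a whole.** This is true if every criterion is judged in a single sitting. It does not show that they have to be. The objection stands for adherence and for therapy that is the other arm's treatment.
- **PP2 is supplementary.** This stands. A reader might infer that unmasked review endangers the trial's non-inferiority conclusion. The documents do not support that: ITT is primary, and neither PP1 nor the CACE models are described as using this review. A distorted PP2 might also show up as a divergence from them.
- **Outcome blinding is already promised.** This stands. A reader might infer that the promise is hollow because the PHQ-9 is recorded at every session attended. But sessional scores are outcome data, so the stated rule already requires them to be withheld. How that is done belongs to the analysis plan or working procedures.
- **Adherence could simply be reduced to a masked pass/fail flag from the supervisors' forms.** This would remove less than it seems to. Those ratings come from supervisors who know the therapy, the article gives no cut-off, and it does not say that PP2 uses these forms. Cut-offs on two different scales could themselves be unequally strict. The point does not rely on such a flag.
- **The size is assumed, and exclusions could differ by arm under full masking** if attendance or adherence truly differs. Both stand. The figures show what uneven exclusion can do, not how much of it unmasking would cause.

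**Conclusion.** The point holds in a limited form. Declaring the whole PP2 review unblind goes further than its criteria require: session number and timing, and most additional therapies, can be judged masked. The consequence is a possible bias in the PP2 estimate alone, in either direction, and so a weaker check on ITT. It would be too strong to say that PP2 cannot corroborate the ITT result, because outcome blinding bars direct selection on results and gives PP2 some protection.

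The size cannot be derived from the documents. The illustrative 0.14 to 0.60 points (7% to 30% of the margin) rests on an assumed net imbalance of 5 to 20 exclusions and an assumed one-SD deficit in each excluded patient; only the SD, the 250 per arm and the margin are the plan's own. The absence of operational rules for PP2 from the article is no finding, since it refers to the analysis plan for them. The masking statement is a finding because the article fixes it. This is a worthwhile, inexpensive improvement to a supplementary analysis.

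**What to change.** Replace the masking sentence for PP2 with a two-stage review.

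1. **Masked stage.** Decide and lock exclusions for session number, session timing and additional therapies from a listing without arm, therapist or any outcome field, including sessional PHQ-9. Carry forward to stage two any case in which the additional therapy is the other arm's treatment.
2. **Unmasked stage.** Assess adherence with the arm known, using criteria set beforehand for each therapy, still blind to outcome. Lock these decisions before outcomes are linked.
3. **Reporting.** Give the number of exclusions and the reasons by arm and by stage. Repeat PP2 with the patients excluded only at the unmasked stage restored, so that the effect of the unmasked judgements can be seen.
4. **Reconcile with Blinding.** State how PP2's planned unblinding fits the rule that assignment is unmasked only on the committee's direction.

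The cost is a little extra listing work and the setting of adherence criteria in advance; no new data are needed. The downside is that a case is not seen as a whole in the first stage.

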### Secondary analysis

This will consider baseline to 6-month and baseline to 12-month change in PHQ-9, BDI-II, CORE-OM, GAD-7, WSAS, and EQ-5D-5L and QoLS using the same methodology as for the primary outcome measure. Similarly, change from baseline to the routinely collected end of therapy score on PHQ-9, GAD-7 and WSAS will be analysed. The proportions of patients making reliable and clinically significant change [56, 57] on PHQ-9, BDI-II, CORE-OM and GAD-7 will also be compared. Additional exploratory analyses will be used to identify characteristics of patients and therapists that are predictive of better outcomes overall and within each therapy. In addition, the reasons why patients leave therapy prematurely and the experiences of patients who remain in or leave therapy will be investigated. Consideration will also be given to the number and effect on outcome of patients experiencing sudden gains in each treatment arm.

### Routine service data for patient cohort

For the period spanning patient recruitment into the trial (approximately 36 months), all patients who are stepped up to step 3 will define the patient cohort within which the trial is embedded. Data collected routinely as part of the service for non-trial participants will be made available in anonymised form as a comparator. These data will provide added value in terms of external validity and will allow comparisons to be made between trial participants and non-participants, in order to consider the representativeness of our research sample. The ability to derive this comparison addresses a key limitation of trials methodology in terms of external validity.

Given that the primary outcome measure is standard throughout IAPT services, the outcomes of trial and non-trial patients can be compared with those from published literature on counselling and CBT within routine IAPT services [2–4, 58]. This approach does not place any additional burden on non-trial participants, as the measures they complete are routine and mandatory as part of the IAPT service agreement. Further, it does not add cost to the proposed study and therefore is clear added value. In addition, as the data will contain sessional PHQ-9 scores including a last session attended (end of therapy) score, it will be used in conjunction with trial data for further analyses.

### Missing data

By recruiting sufficient numbers to account for trial dropout to 6-month follow-up, it is planned that primary endpoint data will be adequate to address the main research question. Routinely collected PHQ-9 scores will be available for sessions attended prior to dropout, and these will be used as part of the imputation process where the 6-month endpoint data are missing. It is expected that 80% of patients who have competed treatment will provide research data at 12 months post-randomisation. Isolated instances of missing data will be imputed by linear interpolation. Multiple imputation methods will be used for patients with more substantial missing data, and the sensitivity of the results will be further assessed by imputing alternative values based on the reason for dropout.

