#### Secondary Outcome Measures

A range of secondary outcome measures is collected. At baseline, the intensity of depression is measured via the Beck Depression Inventory-II (BDI–II) [42], psychological distress via the Clinical Outcomes in Routine Evaluation-Outcome Measure (CORE-OM) [43], generalised anxiety via the Generalised Anxiety Disorder Assessment (GAD-7) [44], plus the Work and Social Adjustment Scale (WSAS) [45]. Mobility, self-care, usual activities, pain/discomfort and anxiety/depression are measured via the EQ-5D-5L [46, 47] and Quality of Life Visual Analogue Scale (QoLS) (personal communication: [name]). In addition, patients complete the Connor-Davidson Resilience Scale (CD-RISC) [48]. Patient service receipt data are also collected [49]. At 6- and 12-month follow-ups, in addition to the PHQ-9 as the primary outcome, the BDI-II, CORE-OM, GAD-7, WSAS, EQ-5D-5L, QoL and CSRI are collected, as is the Client Satisfaction Questionnaire (CSQ) [50].

Four weeks after a patient ends treatment, either through completing or dropping out from sessions, they are contacted to undertake a brief questionnaire/short interview (telephone, face-to-face or web-based) to collect data on their experiences of the treatments.

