### Sample Size

Published findings [2–4] and Sheffield IAPT service data (1/4/09 – 30/9/10) indicate only small differences in outcomes between CBT and counselling. Hence, from these findings we predict the actual difference in mean change between treatments to be zero. Accordingly, the margin within which CBT could not be considered statistically or clinically more effective than CfD was determined as follows: First, treatment effects of 0.2 to 0.3 are conventionally viewed as ‘small’ and of limited clinical value (e.g., [51, 52]). Second, it has been recommended that the threshold for non-inferiority be set at 50% or less than the expected difference between CBT and usual care, which would mean an effect size of less than 0.3 (i.e., 0.6/2). Finally, discussions with psychologists on the research team and IAPT staff indicated that less than 2 points on the PHQ-9 is not perceived as clinically important, which is equivalent to an effect size of just under 0.3 (given the pre-last SD of 6.9 found in the service data above). Therefore, a pre-last change difference of less than 2 on PHQ-9 in favour of CBT was adopted as the limit for non-inferiority of CfD.

It is estimated that 550 patients (275 per arm) would need to be recruited to the trial to secure the 500 patients needed to test the non-inferiority hypothesis at the one-sided 2.5% significance level with a power of 90%. This assumes a standard deviation of 6.9 (derived from the aforementioned service use data, which incorporate both inter-patient and inter-therapist variability), no underlying difference between the effect of CBT and counselling and a 10% loss to 6-month follow-up. As the trial is within a service with few additions to routine practices and procedures, it is expected that relatively few participants will leave the trial and not provide a 6-month follow-up PHQ-9. To sustain adequate referrals via PWPs, weekly monitoring of referral rates in each sector occurs together with monthly feedback via sector managers as well as target setting.

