### Process Analyses

To achieve a fuller understanding of patients’ experiences of CBT and CfD and how these impact of the course of treatment, we will carry out a programme of process studies using a defined sampling frame comprising cases of therapy non-completion and accounts of positive change (based on questionnaire returns and selective interviews); patient engagement, resilience and therapeutic alliance (based on a subsample of routinely collected tapes); and the phenomenon of sudden gains and deteriorations (based on routinely collected sessional PHQ-9 scores). We will also be investigating therapy non-completion and accounts of change through telephone or face-to-face interviews with consenting participants who have dropped out of therapy.

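### The one named missing-outcome sensitivity analysis works by reason for dropout and is not set up to show how much worse missing CfD patients must be before the −2 limit is crossed

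*Protocol article*

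**What the plan says.** The Missing data section of the protocol article plans linear interpolation for isolated gaps and multiple imputation for larger ones, drawing in part on the PHQ-9 scores recorded at therapy sessions. It then adds a single sensitivity analysis: "the sensitivity of the results will be further assessed by imputing alternative values based on the reason for dropout". It does not say where the reason comes from, which values are used, or whether they differ by arm.

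Elsewhere the article describes gathering reasons in connection with therapy. The Objectives and Secondary analysis sections speak of reasons for leaving treatment early. Process Analyses plans "telephone or face-to-face interviews with consenting participants who have dropped out of therapy". Secondary Outcome Measures describes an exit contact: "Four weeks after a patient ends treatment, either through completing or dropping out from sessions, they are contacted". Its stated content is the patient's experience of treatment, and it covers completers as well as dropouts. No section links either contact to the imputation.

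Under Primary analysis, non-inferiority is concluded "if the CI lies entirely above the non-inferiority limit of −2 units". The sample size allows for "a 10% loss to 6-month follow-up".

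**The concern.** Two events are involved. One is leaving therapy, for which the article describes collecting reasons. The other is having no 6-month PHQ-9, which is what must be imputed. They overlap but are not the same. A patient who leaves therapy may still return the 6-month questionnaire. A patient who completes therapy may not, and for that patient no reason for leaving therapy exists. Where a reason does exist, its collection as described relies at least partly on the patient answering a contact or consenting to an interview.

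The primary conclusion is also one-sided. Missing data threaten it if unobserved CfD patients did worse than the imputation assumes, relative to unobserved CBT patients. A useful stress test moves the imputed CfD scores in that direction and reports when the conclusion changes. Values keyed to reasons, with no stated shift against CfD, do not produce that figure. The per-protocol and CACE analyses do not supply it either, because they deal with treatment received rather than missing outcomes.

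**Working it through.** **Inputs.** From Sample Size: "test the non-inferiority hypothesis at the one-sided 2.5% significance level with a power of 90" per cent; "This assumes a standard deviation of 6.9"; "no underlying difference between the effect of CBT and counselling and a 10% loss to 6-month follow-up"; 500 patients needed and 550 recruited (275 per arm). From Primary analysis: the limit of −2. Differences are CfD minus CBT in improvement, so negative values favour CBT.

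**The plan's own figure.** n per arm = 2 × (1.960 + 1.282)² × 6.9² / 2² = 250.2, rounded up to 251 (502 in total). The stated 250 per arm gives power of 90.0%. The plan's figure is reproduced. Recruiting 550 and losing 10% leaves 495, with power of 89.7%.

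**Tipping shift.** Let m be the share of outcomes missing, equal in both arms. Suppose that before any shift the imputed analysis gives the observed difference d. Worsening every imputed CfD score by δ lowers the CfD mean by m × δ. The lower confidence limit reaches −2 when

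δ = (2 + d − h) / m, where h = 1.96 × 6.9 × √(2 / n_obs) and n_obs = 275 × (1 − m).

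- At m = 10%: n_obs = 247.5 and h = 1.216. With d = 0, δ = (2 − 1.216) / 0.10 = 7.8. With d = −0.5, δ = (1.5 − 1.216) / 0.10 = 2.8.
- At m = 20%: n_obs = 220 and h = 1.289. With d = 0, δ = (2 − 1.289) / 0.20 = 3.6. With d = −0.5, δ = (1.5 − 1.289) / 0.20 = 1.1.

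| Missing per arm | h | d = 0 | d = −0.25 | d = −0.5 | d = −0.75 |
|---|---|---|---|---|---|
| 10% | 1.216 | 7.8 | 5.3 | 2.8 | 0.3 |
| 20% | 1.289 | 3.6 | 2.3 | 1.1 | not shown even with no shift |

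Entries are PHQ-9 points by which missing CfD patients would have to be worse than imputed.

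**Which cells matter.** The cell at d = 0 and 10% missing uses the planning values. The other differences and the 20% share are assumptions. They are not remote: the two service data sets under Pilot work and determining type of trial run from 0.5 points in favour of counselling to 1.0 point in favour of CBT. For 12 months, the Missing data section expects data from 80% of those who complete treatment, so at least 20% missing is credible at that time point.

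**Simplification.** h is held fixed at the observed-data value. Good use of session scores in the imputation would narrow it. The extra spread that a shift creates in the CfD arm would widen it a little.

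**The case against.** The strongest reply is that this is detail for the analysis plan, which is not shown. The article is a condensed account; the source of the reason, the treatment of unknown reasons and the values used could all be set out there. This stands as far as those details go. What remains is that the article does commit to a method, and the method it names is not the one that answers the non-inferiority question.

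A reader might infer more than the text supports:

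- **That the reasons come from the exit contact, so the rule has no input for the patients who matter.** The article names no source. Type of therapy ending was available in an earlier data set from the same service, and the Missing data section opens by speaking of dropout from the trial, so its reason for dropout may be meant that way. No figure shows that patients without a 6-month score are the least likely to answer the exit contact. Unknown reason could be its own category, with unfavourable values.
- **That reason-based values are common to both arms and so pull the arms together.** The text does not say they are common. Even a common rule would separate the arms if the mix of reasons differed.
- **That the article's own warning about groups looking artificially similar applies here.** That warning, under Primary analysis, concerns dilution in the intention-to-treat analysis when treatment is not delivered as planned, not imputation.

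It is also fair to say that 7.8 points exceeds the whole mean pre-last change of 6.8 in the service data, that reason-based scenarios are a legitimate departure from missing at random, and that the separate analysis of end-of-therapy PHQ-9 gives a comparison that does not need a 6-month response. All of this stands. It limits the weight of the point without supplying the missing tipping figure.

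**Conclusion.** The point holds in a limited form. The only missing-outcome sensitivity analysis the article names rests on reasons that, as their collection is described, concern leaving therapy and need not exist for or explain a missing 6-month PHQ-9. It states no shift against CfD. It is therefore not set up to show the departure at which non-inferiority would be lost; it would be too strong to say that it cannot test the result at all.

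The size depends on the data. With no observed difference and 10% missing, the conclusion would survive any plausible shift. With an estimate leaning modestly towards CBT, or with loss at 20%, a shift of about 1 to 4 points would be enough, and readers would want to see that number. These figures assume SD 6.9, 275 randomised per arm, equal missing shares, a shift applied to all imputed CfD scores and a fixed interval width. The point is an improvement worth making before analysis; it does not show that the planned conclusion would be wrong.

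**What to change.** Keep the reason-based scenarios as a supplement and add an arm-specific delta-adjusted multiple imputation that does not use the reason. Starting from the planned imputation, worsen imputed CfD scores in steps, leave imputed CBT scores unchanged, and report the shift at which the lower limit crosses −2. Do this for PHQ-9 at 6 months, and at 12 months as a secondary result. Suggested wording: 'As a sensitivity analysis for missing PHQ-9 scores, imputed values in the CfD arm will be worsened by increasing amounts, with imputed values in the CBT arm unchanged, and the smallest shift at which non-inferiority is no longer shown will be reported.'

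The cost is a few more runs of an imputation already planned and one more result to report. No new data are needed, and the article states that recruitment was still under way, so the change can be fixed before analysis.
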